### Sample size calculation

2.7

A recent meta-analysis assessing the effect of CBT-I in patients with insomnia and comorbid psychiatric disorders (MDD, PTSD, and alcohol and hypnotic dependence), found medium to large effect sizes (*d* ≥ 0.5) on psychiatric symptoms (Wu et al., 2015). This meta-analysis contains both studies with an active (e.g., sleep diary, sleep hygiene only) or inactive (e.g., waiting list, care as usual) control condition. Using linear mixed models to estimate treatment effects averaged over T1 and T2, based on a medium effect size (Cohen's *d* = 0.5) on our primary outcome BPD severity, α = 0.05, power = 0.80 and correlation among repeated measures = 0.5, 48 patients per condition are needed.

### Analyses

2.8

For all outcomes, we will fit linear mixed models to estimate effects of time and the interaction between time and treatment allocation, while omitting the main effect of treatment allocation to control for baseline differences. The outcome measures are structured hierarchically because of the repeated measures nested within subjects. The effect of interest for establishing the effectiveness of iCBT-I is represented by the two time by treatment allocation terms. In post-hoc analysis we will analyze whether the effect on BPDSI score mainly results from iCBT-I alone (comparing T0 with T1) or the combination of iCBT-I and STEPPS (comparing T0 with T2 and adding measurements at T1 as moderators). Possible effect modification of individual differences in several mental health predictors (baseline severity of insomnia, anxiety, and depression symptoms) are assessed by adding them as predictors together with their interaction with treatment allocation. We will conduct intention-to-treat analyses. Assumptions underlying our planned analyses will be checked and reported. Sleep diary data and EEG data will both be aggregated into weekly and 4-night averages respectively. Analyses will be carried out in R using α = 0.05 for all significance tests.

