#### STEPPS

2.3.2

STEPPS is a 20-week manual-based group treatment for patients with BPD symptoms (Blum et al., 2008). STEPPS is a cognitive-behavioral skills training approach characterizing BPD as a disorder of emotion and behavior regulation. STEPPS aims to improve emotion regulation by becoming more aware of thought patterns, feelings, and behaviors that define BPD, and to acquire emotion and behavior management skills. Patients receive individual treatment parallel to group treatment, mostly to guide homework exercises and provide personal guidance. STEPPS is delivered by trained clinicians working at GGZ InGeest. At some locations of the trial a shortened 10-week version of STEPPS is offered, which is a practice-based adaptation of the 20-week version, including the same goals and core features (Freije, 2016). STEPPS is tested in several RCTs showing moderate to large effects sizes on BPD symptoms (Blum et al., 2008; Bos et al., 2010).

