### Randomization

2.6

To guarantee blindness during baseline diagnostic interviews, patients are randomized only after T0 assessments, by an independent researcher. Simple randomization is applied for the first 10 patients. To ascertain balanced, equally sized groups, subsequent patients are assigned using covariate adaptive randomization (group size, sex, age, use of psychotropic medication (current/past/never), time of year of inclusion (week number), baseline severity of BPD (BPDSI and BPD-C scores), insomnia (ISI scores), depression and anxiety (RMT-20 scores), duration of STEPPS (10 or 20 weeks), and diagnosis (BPD or other PD with ≥4 BPD traits)) scripted in R and carried out by an independent researcher. Covariate adaptive randomization is a minimization randomization method which minimizes imbalance on selected factors (covariates) and is in line with the CONSORT statement, which describes this method as equivalent to general randomization (Schulz et al., 2010). Due to the nature of the intervention, the therapist is not blind to treatment condition. The primary outcome measurement (BPDSI) is administered by a blinded and trained researcher. In addition, EEG data is scored by a trained researcher who is blind to experimental condition. All other outcome assessments involve self-report questionnaires that remain blinded. For analysis, all data is re-coded regarding participant number and condition to ensure blinding.

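### Allocation is minimised on about ten baseline covariates, but the stated model adjusts only for the analysed outcome's own baseline; if the other factors are prognostic, the test is conservative and some power is lost

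*Protocol article*

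**What the plan says.** Randomization (2.6): the first 10 patients are simply randomised. Later patients are minimised on "group size, sex, age, use of psychotropic medication (current/past/never), time of year of inclusion (week number"). The list goes on with "baseline severity of BPD (BPDSI and BPD-C scores), insomnia (ISI scores), depression and anxiety (RMT-20 scores), duration of STEPPS (10 or 20 weeks"). Its last entry is the type of diagnosis. Apart from group size, that makes ten baseline covariates: sex, age, medication, week of inclusion, BPDSI, BPD-C, ISI, RMT-20, STEPPS duration and diagnosis.

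STEPPS (2.3.2): the duration factor exists because "At some locations of the trial a shortened 10-week version of STEPPS is offered".

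Analyses (2.8): for all outcomes "we will fit linear mixed models to estimate effects of time and the interaction between time and treatment allocation". The treatment main effect is dropped so that baseline differences are handled, which makes this a constrained-baseline model. Baseline insomnia, anxiety and depression appear only in separate effect-modification models. No minimisation factor is named as a covariate in the main model. On the level, "Analyses will be carried out in R using α = 0.05 for all significance tests".

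Sample size calculation (2.7): the target quantity is given as "Using linear mixed models to estimate treatment effects averaged over T1 and T2". The effect assumed for it is a Cohen's d of 0.5 on BPD severity, and the remaining inputs and the result read "power = 0.80 and correlation among repeated measures = 0.5, 48 patients per condition are needed".

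**The concern.** Minimisation makes the arms more alike on the chosen factors than chance would, so the treatment estimate varies less from trial to trial. An analysis that leaves those factors out does not register this. The variation they explain stays in the residual, and the reported standard error describes a less balanced trial than the one that was run. The interval is then wider than it needs to be, the test rejects less often than 5% under the null, and some power is given up.

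The constrained baseline removes this problem for one factor in each model, the T0 score of the outcome being analysed. In the primary analysis that factor is BPDSI, presumably the strongest predictor. The other nine covariates remain outside the primary model. In the models for secondary outcomes, T0 BPDSI is outside as well.

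**Working it through.** **Inputs from the protocol article.** d = 0.5 (SD 1), α = 0.05 (taken as two-sided), power 0.80, correlation ρ = 0.5, effect averaged over T1 and T2, 48 per arm.

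**Assumptions.** Compound symmetry and no drop-out. R² is the share of the variance left after baseline BPDSI that the other minimisation factors explain. The documents give no value, so a range is shown.

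**1. The plan's own figure.** The mean of two visits has variance factor (1 + ρ)/2 = 0.75. Then n = 2 × 0.75 × (1.960 + 0.842)² / 0.5² = 47.09, so 48 per arm, with power 0.807 (0.799 using the t distribution). The stated 48 reproduces. A change-from-baseline analysis has the same factor of 0.75 at ρ = 0.5, so this sizing takes no net gain from any covariate.

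**2. The model in 2.8.** With the constrained baseline the factor is (1 + ρ)/2 − ρ² = 0.75 − 0.25 = 0.50. SE = √(0.50 × 2/48) = 0.1443, and generalised least squares on the three visits gives the same value. Power for the averaged effect is Φ(0.5/0.1443 − 1.96) = 0.934. Under the same inputs, a 2-df joint test of the two interaction terms has power 0.883 and each single term 0.807.

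**3. Omitting the other factors, under perfect balance.**
- The reported SE stays at 0.1443 while the true SD is 0.1443 × √(1 − R²), so the SE is too wide by 1/√(1 − R²).
- Type I error = 2[1 − Φ(1.96/√(1 − R²))].
- Power unadjusted = 1 − Φ[(1.96 − d/0.1443)/√(1 − R²)].
- Power adjusted = Φ[d/(0.1443 √(1 − R²)) − 1.96].

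| R² | SE too wide by | Type I error | Power at d = 0.5, unadjusted → adjusted | Power at d = 0.4, unadjusted → adjusted |
|---|---|---|---|---|
| 0 | 0% | 0.050 | 0.934 → 0.934 | 0.791 → 0.791 |
| 0.10 | 5.4% | 0.039 | 0.944 → 0.955 | 0.804 → 0.832 |
| 0.20 | 11.8% | 0.028 | 0.954 → 0.972 | 0.818 → 0.873 |

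**4. Check by simulation.** 96 patients, the first 10 simply randomised, then minimisation on ten covariates with an assumed assignment probability of 0.85, 4,000 runs per setting.
- R² = 0.20: mean SE 0.144 unadjusted against 0.130 adjusted; type I error 0.032 against 0.048; power at d = 0.5 of 0.940 against 0.967.
- R² = 0.10: type I error 0.039 against 0.046; power 0.938 against 0.949.
- R² = 0: power 0.926 against 0.921, so adjusting for nine useless covariates costs about 0.5 point.

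A separate simulation with eight factors plus the baseline outcome gave, at d = 0.4, power of 78% against 81% (R² = 0.10) and 80% against 86% (R² = 0.20).

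**5. How the covariates must enter.** In a constrained-baseline model T0 is part of the response. A covariate with one time-constant coefficient is therefore forced to act equally at T0, T1 and T2. If a factor acts only after baseline, that form recovers about 13% of the variance where 20% is available, and about 6% where 10% is available. The gains in step 3 need the covariate-by-time interaction.

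**The case against.** The strongest reply is that this is a condensed article, that a covariate list can be left to a statistical analysis plan, and that 2.6 promises balance, not adjustment. This stands in part: a plan that is not shown could add the covariates. But 2.8 is not silent. It states the model's terms for all outcomes and names the one term to be dropped, so the model as written has no other covariate.

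A second reply concerns size, and it largely stands. The loss exists only if the factors add to baseline BPDSI. The R² values are not small either: if the factors act equally at all visits with ρ = 0.5, an R² of 0.10 needs them to explain about 17% of total BPDSI variance, and 0.20 about 29%. At the planned d = 0.5 the gain is modest.

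Against that, 0.934 is a favourable case: averaged effect, full d, no drop-out. Section 3.1 itself calls the effect-size estimate indirect and names drop-out as a risk, and 2.4 lets recruitment end early if funding requires it. So the d = 0.4 column is relevant.

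A reader might also infer that T2 falls about 6 weeks after a 20-week STEPPS course and about 16 weeks after a 10-week one (34.8 − 28.7 and 34.8 − 18.7 weeks), making duration a known source of T2 variance. That assumes STEPPS starts immediately at T1. The protocol does not fix this: patients are on a waitlist, and T1 is only ideally before STEPPS. The documents do not quantify any effect of duration.

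**Conclusion.** The mismatch between allocation and analysis is real, and its consequence is conditional and conservative. Apart from the analysed outcome's own T0 score, no minimisation factor is in the stated model. If the factors are prognostic beyond that score, with R² of 0.10 to 0.20, type I error is about 4% to 3%. The power forgone is about 1 to 2 points at d = 0.5 by the formulas (up to 2.7 in the simulation) and about 3 to 6 points at d = 0.4. At R² = 0 nothing is lost by leaving them out. These figures rest on a two-sided test, compound symmetry with ρ = 0.5, no drop-out and the assumed R².

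A reader might infer that the trial is underpowered or that its type I error is wrong in the harmful direction. The documents support neither. The 48 per arm reproduces without any net covariate gain, the planned model exceeds 80% power for the averaged effect under the plan's own inputs, and the omission does not inflate type I error. This is a worthwhile, nearly free improvement, not a defect that threatens the conclusion.

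**What to change.** In 2.8, prespecify the main minimisation factors as fixed covariates in the primary and secondary models: sex, age, psychotropic medication, diagnosis, STEPPS duration, and T0 BPDSI, BPD-C, ISI and RMT-20. Give each its interaction with time so that it can act after baseline; this matters for STEPPS duration in particular. Keep the constrained baseline, and leave out of each outcome's model that outcome's own T0 score, which would otherwise be both response and covariate. State whether week of inclusion is adjusted for. Report the unadjusted model as a sensitivity analysis.

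The cost is a few sentences, and every variable is already collected before randomisation. In the BPDSI model the list takes about nine between-patient degrees of freedom out of 96 patients (two for three-level medication and one for each of the other seven, counting RMT-20 as one score). If the factors prove not to be prognostic, the power lost is about 0.5 point. Fixing the list now also prevents covariates from being chosen after the results are seen.

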**Fig. 2 f0010:**
[figure not shown]
Schedule of enrolment, interventions, and assessments. Note. T1 and T2 are 2 months and 8 months after baseline respectively. Use of medication and treatment is additionally assessed between T1 and T2; at 4 months and 6 months.

Subsequently, patients commence with the T0 assessment, which contains all outcome measures and an online baseline survey. All outcome assessments are repeated at T1 (2 months after T0, after either iCBT-I and ideally before STEPPS starts, or waitlist) and T2 (8 months after T0, after STEPPS). Use of psychotropic medication and psychotherapeutic treatment is additionally assessed at 4 and 6 months after T0. After T0, patients are randomly assigned to iCBT-I group or the sleep diary-keeping control group. During all phases of the trial, there is one central contact person to provide support to all patients. After completion of the trial, patients in the control condition will be offered identical treatment of remaining sleep problems.

Patients may withdraw from participation at any time, for any reason, without consequences for their awaited treatment. We aim to perform intention-to-treat analyses, so patients that decide to withdraw from treatment are asked to continue the outcome assessments. We will continue recruitment until the intended sample size is achieved or until funding restrictions compel us to end assessments. Data of patients that withdraw from participating are used and reported, unless patients ask us to destroy any data.

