### Strengths and limitations

3.1

The study has several strengths. First, administering iCBT-I prior to standard BPD treatment allows us to study the direct effect of iCBT-I on BPD symptomatology (at T1) and the synergistic effect with standard emotion regulation therapy (at T2). Second, a particular methodological strength is the vast variety of thoroughly assessed outcome measures. BPD severity is assessed through clinical interview as opposed to mere self-report. In addition, sleep parameters are assessed both subjectively and objectively, including physiological sleep measures through ambulatory EEG. This allows for an in-depth analysis of sleep factors moderating clinical outcome. The wide array of secondary outcome measures, including emotion regulation, anxiety and depressive symptoms, quality of life and daytime functioning, allows us to compare results with currently running studies testing the effect of iCBT-I in other psychiatric disorders. Finally, due to the accessibility of the studied intervention, any positive findings of our RCT can be readily implemented in clinical practice.

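### The post-hoc analysis in 2.8 that adds T1 measurements as moderators cannot show whether the iCBT-I effect grows during STEPPS

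*Protocol article*

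**What the plan says.** The Protocol article, section 1.2, sets out a two-part hypothesis: BPD symptoms improve directly after iCBT-I, and improve further after STEPPS through synergy. Section 3.1 lists as the first strength that the design allows study of the direct effect at T1 and of "the synergistic effect with standard emotion regulation therapy (at T2".

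Section 2.8 fits a mixed model with time and time-by-allocation terms and no main effect of allocation. Effectiveness is judged on the two time-by-allocation terms. A post-hoc step on BPDSI then compares T0 with T1 for iCBT-I alone, and addresses "the combination of iCBT-I and STEPPS (comparing T0 with T2 and adding measurements at T1 as moderators". The text does not name the T1 measurements or the coefficient that decides. The following sentence describes effect modification by baseline severity measures as a predictor plus its interaction with allocation.

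Section 2.4 places randomisation after T0 and T1 at "2 months after T0, after either iCBT-I and ideally before STEPPS starts, or waitlist". Under 2.1, both arms go on to STEPPS.

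**The concern.** A moderator has to be fixed before treatment, or at least be unaffected by it. T1 is neither: it is measured after iCBT-I, and section 1.2 predicts an effect there. Conditioning the T2 comparison on T1 removes only the part of the early gain that T1 predicts. The rest of a purely persistent iCBT-I effect stays in the treatment coefficient and could be taken for something that arose during STEPPS.

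At stake is the second half of a stated hypothesis, and a claim that the article presents as a strength of the design. The step is labelled post-hoc, but it is the only analysis the article describes for separating the two parts.

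**Working it through.** **Inputs.** From 2.7: d = 0.5, correlation 0.5 among repeated measures, α = 0.05, power 0.80, 48 per arm. Assumed: two-sided tests, unit SD at each visit, complete data, and BPDSI as the T1 measurement. Negative values favour iCBT-I.

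**1. The plan's own figure.** The sizing target is "Using linear mixed models to estimate treatment effects averaged over T1 and T2, based on a medium effect size". The variance of a two-visit mean is (1 + 0.5)/2 = 0.75. Then n = 2 × (1.960 + 0.842)² × 0.75 / 0.5² = 47.1, so 48 per arm. The figure reproduces.

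**2. Scenario.** The arm difference is −0.5 SD at T1 and the same at T2. Nothing is added during STEPPS.

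**3. Reading A: T2 regressed on allocation, T0 and T1.**
- Partial slope of T2 on T1 given T0: (ρ − ρ²)/(1 − ρ²) = 0.25/0.75 = 1/3.
- Treatment coefficient: −0.5 + 0.5/3 = −0.33 SD.
- Residual variance of T2: 1 − 2ρ²/(1 + ρ) = 2/3. SE ≈ √{(2/3) × [2/48 + 0.5²/(0.75 × 93)]} = 0.174. The ratio is 1.92, so rejection is about 47%.
- Simulation (8,000 trials): −0.34 SD, 48%. A model with a centred T1-by-allocation term gives the same for its main effect. If T1 is left uncentred, with its mean 2 SD above zero, that main effect rejects in 16%.

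**4. Reading B: the T2 − T0 change regressed on allocation and T1.**
- Slope of the change on T1: 0.5 − 0.5 = 0, so the adjustment removes nothing and the coefficient is −0.50 SD.
- SE ≈ √(2/48 + 0.5²/94) = 0.211. The ratio is 2.37, so rejection is about 65%. Simulation: −0.50 SD, 65%.

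**5. Reading C: the T1-by-allocation interaction.** With no growth, its mean is 0.00 and it rejects in 5.0%. With real growth of 0.25 SD (0.5 to 0.75) or 0.50 SD (0.25 to 0.75), it still rejects in only about 5%. It tests whether the T1-T2 relation differs by arm, which is another question.

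**6. Sensitivity to correlation** (no growth, −0.5 SD at both visits):

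| Correlations T0-T1, T1-T2, T0-T2 | Reading A rejects | Reading B rejects |
|---|---|---|
| 0.3, 0.3, 0.3 | 48% | 51% |
| 0.5, 0.5, 0.5 | 48% | 65% |
| 0.7, 0.7, 0.7 | 53% | 85% |
| 0.7, 0.8, 0.6 | 18% | 66% |

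In the last row the slope for A is (0.8 − 0.42)/(1 − 0.49) = 0.75, so more of the early gain is removed.

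**7. Sensitivity to the effect.** With no effect at either visit, A rejects in 5.0%. If 0.5 SD fades to 0.17 SD, A gives 0.00 and hides the loss. If it halves to 0.25 SD, A gives −0.25 + 0.5/3 = −0.08, again without showing that benefit was lost.

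**8. The alternative: T2 effect minus T1 effect.** With no growth, its mean is 0.00 and it rejects in 5.2%. Its variance is 2(1 − 0.5) × 2/48, so SE = 0.204 and the 95% half-width is about 1.96 × 0.204 = 0.40 SD. Power for an added 0.25 SD: ratio 1.22, about 23% (simulation 24%). For an added 0.50 SD: ratio 2.45, about 69% (simulation 68%).

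**The case against.** The strongest defence is that the article does not commit to the model that misleads. Taken literally, and in line with the sentence that follows it, a moderator is a predictor with its interaction with allocation, and that test holds its 5% level. The T1 measurements might also be sleep variables, since 3.1 speaks of sleep factors moderating outcome. The slope of 1/3 does not carry over to those, because the article gives no correlation between sleep and BPDSI. The full protocol may settle both choices.

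This stands as a limit on the size of the problem. It does not rescue the clause: under the interaction reading the analysis is uninformative about growth, and no T1 variable that treatment has changed isolates a STEPPS-phase effect by being conditioned on.

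A reader might infer three stronger things that the document does not support:
- *That the plan will report a STEPPS effect where none exists.* This needs T1 BPDSI as the covariate, an early effect that largely persists, and a conclusion drawn from the treatment coefficient.
- *That the trial's main result is compromised.* Effectiveness rests on the two time-by-allocation terms without T1 adjustment, and the T2 comparison is a valid randomised comparison of the two treatment sequences.
- *That T1 is contaminated by STEPPS.* The text says only that T1 ideally comes first and gives no count of exceptions.

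**Conclusion.** The point holds for the post-hoc analysis only. T1 is a post-randomisation outcome that iCBT-I is expected to change, and using it as a moderator of the T0-T2 comparison cannot separate a maintained benefit from an added one. Depending on the reading, the step can label a maintained 0.5 SD effect as an added one in about 48% to 65% of trials at the protocol's correlation and sample size, or it has no useful power for growth. The first figures rest on the assumptions listed above and fall to 18% for one model form under one unequal-correlation pattern.

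A separate limit comes from the design. Both arms receive STEPPS, so no model for T2 identifies synergy. Growth of the arm difference could be delayed benefit of iCBT-I, and a flat difference would not exclude synergy if the effect would otherwise have faded. The T2-minus-T1 contrast therefore describes the course of the arm difference and not its cause.

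**What to change.** - **Section 2.8.** Replace the clause on T1 moderators by the difference between the T2 and T1 time-by-allocation coefficients of the planned mixed model, reported with a 95% confidence interval. Describe it as showing whether the arm difference grows, holds or shrinks over the STEPPS period. State its power at 48 per arm: about 24% for an added 0.25 SD and 68% for 0.50 SD. A non-significant contrast should not be read as no growth.
- **Any T1-adjusted analysis that is kept.** Label it exploratory mediation, name the T1 variables and the coefficient of interest, and state the assumptions, including no unmeasured common causes of T1 and T2.
- **Sections 1.2 and 3.1.** Describe T2 as iCBT-I followed by STEPPS versus sleep-diary waitlist followed by STEPPS. Synergy may stay as a rationale but should not be claimed as identified.
- **T1 interviews held after STEPPS began.** Report how many by arm. A T1 estimate without them may be shown only as a sensitivity analysis, noting that it selects on a post-randomisation event and could do so differently by arm.

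The cost is wording in three sections. The contrast comes from the model already planned and needs no new data, and the article states that the trial is still open for inclusion. What is given up is a synergy claim that the design cannot support.
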